### Sample size

The trial has three primary endpoints that build on mutually independent hypotheses [140]. Therefore, sample size calculations were performed for each endpoint as described below. All sample size calculations are performed for a significance level of 5%, power of 80%, and a dropout rate of 25%. Ethical approval was obtained for the inclusion of 200 participants in total to ensure enough power for all primary endpoints.
1: Based on a *t* test, a sample size of 120 is required to detect a clinical difference of 3 points (SD=5 points [36]) in MAI score change from baseline to 8 weeks after discharge between the control group and pooled intervention group (MED and MULTI-NUT-MED intervention).2: Based on a paired *t* test, a sample size of 62 participants is required to detect a clinically relevant difference of 4.0 mL/min/1.73m^2^ (SD=15, a R=0.73 [141]) between mGFR and eGFR based on the combination of creatinine and cystatin C. GFR is measured at baseline for all trial participants regardless of group allocation.3: Based on a *t* test, a sample size of 130 participants with or at risk of malnutrition is required to detect a clinically relevant difference of 0.15 points [142] (SD=0.27 [143]) in EuroQol-5D-5L score change from baseline to 16 weeks after discharge between the control group and MULTI-NUT-MED intervention group, assuming equal allocation in the two groups.

Given that patients are included independently of nutrition status and approximately 70% of patients are expected to have or be at risk of malnutrition [4], a total of 185 participants is required to achieve a sample size of 130 participants with or at risk of malnutrition.

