### Aims

The study involving acutely admitted older medical patients has three primary aims (1) to determine whether a medication review intervention is superior to standard care in improving medication appropriateness from admission to 8 weeks after discharge, (2) to determine the accuracy of eGFR equations based on various biomarkers compared to mGFR at a single-time point, and (3) to determine whether an individualized multimodal and transitional nutritional intervention is superior to standard care in improving the quality of life from admission and 16 weeks after discharge.

The study also has the following secondary aims which are related to the effect of the intervention: (1) to measure differences in polypharmacy, PIM use, and assessment of underutilization between the MED-intervention and standard care from admission to 8 weeks after discharge and (2) to measure of the differences in body weight, protein- and energy intake, mobility, cognition, frailty, the intestinal microbiome, and health care costs between the MULTI-NUT-MED intervention and standard care from admission to 8 and 16 weeks after discharge and 1 year after discharge (only health care costs).

Secondary aims, which are based on baseline data or data from the control group, include assessment of (1) how information from a broad pharmacogenetic test can potentially improve medication prescribing appropriateness; (2) how polypharmacy, PIMs, nutritional status, frailty, and inflammation modify the effect of the MED-intervention on prescribing appropriateness; (3) how non-GFR determinants affects eGFR and how the choice of eGFR equation affects medication prescribing; (4) how the choice of malnutrition classification criteria affects the prevalence of malnutrition; and (5) how different definitions of frailty affect the distribution of patients classified as frail or sub-frail as well as the responsiveness of these methods.

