**Fig. 2 Fig2:**
[figure not shown]
Schematic overview of the MULTI-NUT-MED and MED intervention elements and their timeframe. X indicates the timepoint of the intervention element. *These interventions are provided on an individually assessed need. Thus, only the possible timespan of the intervention is indicated. Abbreviations: Multidisciplinary (MULTI), Nutrition (NUT), Medication (MED), and Activities of Daily Living (ADL)

**Table 1 Tab1:** A schematic overview of the study design. Definition of timepoints: t_1_: Within 36 h after admission the ED, t_a_: Immediately after data collection upon enrollment has ended, t_GFR_: During hospitalization or up to 2 weeks after discharge, t_2_: 8 weeks after discharge, t_3_: 16 weeks after discharge, t_1y_: 1 year after discharge. Abbreviations: *GFR* glomerular filtration rate, *MULTI* multidisciplinary, *NUT* nutritional, *MED* medication

Timepoint	Enrollment	Allocation	Post allocation			Close-out
	t_1_	t_a_	t_GFR_	t_2_	t_3_	T_1y_

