### Eligibility criteria, recruitment, and consent

Patients are eligible for inclusion if they are ≥65 years of age, acutely admitted to the ED, community-dwelling, and residing in one of the following municipalities: Hvidovre, Copenhagen (Districts of West and South Western Copenhagen), or Brøndby. Exclusion criteria are inability to understand Danish, inability to cooperate physically (e.g., hearing or speech impairment), or cognitively (e.g., dementia or unconsciousness), isolation room stay, not Caucasian, and admission due to suicide attempt or terminal illness.

Participants are recruited up to 36 h after admission. Each morning (Monday through Thursday), patients are assessed for eligibility from a randomized computer-generated list of all patients in the ED. Eligible patients are informed about the trial both verbally and in writing by a team of seven researchers and are given the possibility of a reflection period of 24 h to consent to participation. Participants are given the option to consent separately to GFR measurement and pharmacogenetic test. After obtaining written informed consent, each participant is randomized to either the intervention group or standard care, and baseline data are collected. After baseline data are collected, each participant is informed about the result of the randomization by staff performing the intervention.

The following strategies are implemented to minimize the effect of staff shortages on patients recruitment: (1) on days with insufficient hospital staff available to perform the MULTI-NUT-MED intervention, only patients with a Mini Nutritional Assessment Short-Form (MNA-SF) [60] score >11 are recruited (to the MED intervention only); (2) on days with insufficient community-based staff available to perform future nutritional intervention (e.g., due to vacation or long term illness), patients from these municipalities are not assessed for eligibility; (3) if more than 35% of the first 50 included patients (*n* = 50) have an MNA-SF score >11, then the project leaders can decide to exclusively recruit patients with an MNA-SF score ≤11 2 days of each week in order to achieve a sufficient number of participants with an MNA-score ≤11 (see the “Sample size” section). The expected recruitment rate is two participants per week for 100 weeks.

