Intestinal microbiome	All participants at risk of malnutrition or with malnutrition according to the nutritional screening tool MNA-SF will collect a fecal sample using EasySampler [129]. Samples collected during hospitalization are frozen as fast as possible at −80°. If collected in the home of the participant, the sample is frozen as fast as possible in the participants own −18° freezer for maximally 3 days. The samples are transferred in a cooler bag with freezer elements to the −80° freezer (Biobank). At the time of collection, the participant reports where the sample belongs on the Bristol Stool Scale [130] and their use of antibiotics.	t_1_, t_2_, t_3_
Blood samples	Blood samples are analyzed for: Alanine aminotransferase, albumin, basic phosphatase, bilirubin, carbon dioxide, C-reactive protein, hemoglobin, coagulation factors II, VII, and X International Normalized Ratio, potassium, urea, coagulation factors, leukocytes, neutrophils, mean corpuscular hemoglobin concentration, mean cell volume, sodium, platelets, lactate dehydrogenase, neutrophil gelatinase-associated lipocalin, BTP and B2M, soluble urokinase plasminogen activator receptor, cholesterols, triglycerides, blood sugar, glycated hemoglobin, insulin, markers of the effect, and plasma levels of medication. Calculation of eGFR will be based on the Chronic Kidney Disease Epidemiology Collaboration [131–133], Berlin Initiative Study [132], Full Age Spectrum [42, 134, 135], Lund-Malmö revised [136], the Caucasian and Asian pediatric and adult subjects [137], Modification of Diet in Renal Disease [138], and Cockcroft-Gault [42] equations based on creatinine, cystatin C, B2M or BTP, or a combination of the markers.	t_1_, t_2_, t_3_, t_GFR_
Health economics	Use of health care services will be collected from the following registries: National Patient Registry, National Health Insurance Registry, The Danish National Prescription Registry [139], and local databases in the municipalities.	t_1-_ t_3_ and t_1_-t_1y_
Descriptive variables	Participant characteristics are based on participant self-report or obtained from the medical journal and include sex, age, civil status, living conditions, education, smoking status, alcohol consumption, physical activity level, use of home- and health care, early warning score and diagnoses.	t_1_

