Timepoint for: baseline: t1, follow-up 8 weeks after discharge: t2, follow-up 16 weeks after discharge: t3, follow-up by telephone 1 year after discharge: t1y, assessment of glomerular filtration rate (GFR): tGFR

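### The sample-size section misstates when and in whom GFR is measured for primary outcome 2, and its figure of 62 matches evaluable pairs with no allowance for the stated 25% dropout

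*Protocol article*

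**What the plan says.** All references are to the protocol article.

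- **Sample size**, item 2: a paired t test needs 62 participants to detect a 4.0 mL/min/1.73 m² difference between mGFR and eGFR from creatinine plus cystatin C (SD 15, R 0.73). It adds that "GFR is measured at baseline for all trial participants regardless of group allocation". The opening of the section sets, for all the calculations, "a significance level of 5%, power of 80%, and a dropout rate of 25" percent.
- **Table 1, timepoint definitions**: baseline, t_1, is "Within 36 h after admission the ED". t_GFR is "During hospitalization or up to 2 weeks after discharge". Kidney function is marked only under t_GFR, a post-allocation column.
- **Table 2**: kidney function is listed at t_GFR only. The footnote defines baseline as t1 and gives a separate label for "assessment of glomerular filtration rate (GFR): tGFR". The blood-sample row, which contains the sentence beginning "Calculation of eGFR will be based on the Chronic Kidney Disease Epidemiology Collaboration", lists t_1, t_2, t_3 and t_GFR.
- **Eligibility criteria, recruitment, and consent**: "Participants are given the option to consent separately to GFR measurement and pharmacogenetic test".
- **Aims**: the accuracy of the eGFR equations is assessed "compared to mGFR at a single-time point".

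**The concern.** Primary outcome 2 is described in two incompatible ways. The sample-size paragraph gives one timepoint (baseline) and one population (everyone). The schedule and the consent procedure give another timepoint (t_GFR) and another population (those who agree).

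Two things follow. First, a reader of the sample-size section would take the accuracy analysis to cover all 200 participants, when it covers a group selected by its own consent. Second, if the group is optional, the reader needs to know whether 62 counts people who agree to the measurement or people with a usable mGFR/eGFR pair. The section says dropout is built in, which points to the first. The arithmetic points to the second.

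**Working it through.** **1. Who and when**

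| Item | Sample size section | Elsewhere in the article |
|---|---|---|
| Timepoint of mGFR | Baseline | t_GFR, in hospital or up to 2 weeks after discharge (Tables 1 and 2); baseline is a different timepoint, within 36 h of admission |
| Population | All participants | Those giving separate consent (eligibility section) |
| Both groups included | Yes | Not contradicted |

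The first two rows conflict; the third does not.

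**2. Reproducing 62**

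Inputs from the Sample size section: difference 4.0, SD 15, R 0.73, alpha 5%, power 80%. Sidedness is not stated, so I assume two-sided.

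- SD of the paired difference = 15 × √(2 × (1 − 0.73)) = 11.02.
- Noncentral-t solution for a paired t test: n = 61.55, rounded up to 62. Power at 62 is 80.3%.
- The normal approximation gives 59.6, so 60.
- Taking 15 as the SD of the difference itself gives 113, which does not match.

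So 62 is reproduced before any dropout is applied.

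**3. Could 62 already contain the dropout?**

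- Two-sided with dropout: 62 / (1 − 0.25) = 82.7, so 83. The cruder 62 × 1.25 = 77.5 gives 78. Neither is 62.
- One-sided: n = 48.33, so 49. 49 / 0.75 = 65.3, which does not match, but 49 × 1.25 = 61.25 rounds up to 62. This is the one route I found by which 62 would include dropout.
- The other two endpoints speak against that route. For MAI (difference 3, SD 5), two-sided gives 45 per group, 90 in total, and 90 / 0.75 = 120, as stated; one-sided gives 72, hence 96 or 90. For EuroQol (0.15, SD 0.27), two-sided gives 52 per group, 104 in total, and 104 × 1.25 = 130, as stated; one-sided gives 82, hence 110 or 103.

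Both companion figures are two-sided and include dropout. On the same two-sided basis, 62 does not include it.

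**4. Consequence for numbers**

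- Needed with 25% loss: 83 consenting participants, and 83 / 200 = 41.5% uptake. With no loss: 62 / 200 = 31%.
- If 62 consent and 25% are lost: 62 × 0.75 = 46.5, about 46 pairs, power 67%.

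Power by assumed uptake among 200 (the article gives no expected uptake):

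| Uptake | Consenting | Power, no loss | Power, 25% loss |
|---|---|---|---|
| 25% | 50 | 71% | 57% |
| 31% | 62 | 80% | 67% |
| 41.5% | 83 | 90% | 80% |
| 50% | 100 | 95% | 87% |
| 75% | 150 | 99% | 97% |

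**The case against.** The strongest reply is that this is a loose sentence in a condensed article and changes nothing in the design. Much of that stands. The schedule in Tables 1 and 2 is clear. Blood for eGFR is drawn at the GFR visit. Only 62, or 83 with loss, of 200 participants are needed, so optional consent does not by itself create a power problem.

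A reader might go further and infer that eGFR from the acute admission would be compared with mGFR measured days or weeks later, so that real change in kidney function would count as equation error. The documents do not support this. The blood-sample row that defines the eGFR calculation lists t_GFR, Table 1 marks blood samples there too, and the aim is a comparison at one timepoint. No passage pairs a t_1 eGFR with a later mGFR. Any estimate of lost power on that basis would also need a within-person variation in GFR that the article does not give. The Statistical methods section does not name the sample used, but an article may leave that to the analysis plan, so the omission is not an error.

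The reply does not remove the contradiction itself. A primary outcome's timepoint and population are stated wrongly, and the text says dropout is included in a figure that, on a two-sided basis, does not contain it. These are misstatements, not details left to another document.

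**Conclusion.** The point holds as an internal contradiction with a modest numerical consequence. The Sample size section is contradicted on both when mGFR is measured and who has it measured. The figure of 62 is best read as evaluable pairs: it reproduces exactly (61.55) with no dropout, and the stated 25% would raise it to about 83. Treating 62 as the number to recruit would leave about 46 pairs and 67% power instead of 80%.

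This rests on a two-sided test, which is not stated for this endpoint but is what the other two sample sizes reproduce, and on dropout applied as n / (1 − 0.25). It does not show that primary outcome 2 is underpowered: with 200 enrolled, uptake of 41.5% or more is enough under the plan's own assumptions. Apart from numbers, the consequence is that the accuracy results describe participants who chose to have GFR measured, which the present wording hides.

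**What to change.** In the Sample size section, replace the sentence on GFR measurement with wording such as: 'mGFR is measured at t_GFR in participants of both groups who consent to it; eGFR for the primary comparison is calculated from the blood sample drawn at t_GFR.' Then state that 62 is the number of evaluable mGFR/eGFR pairs, and that about 83 consenting participants are needed at 25% dropout. State the sidedness of the test; if a one-sided test was meant, show that derivation instead.

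The cost is wording only. The t_GFR blood sample is already in Tables 1 and 2, and neither the total of 200 nor the visit schedule changes.

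### Two of the three sample sizes do not carry the stated 25% dropout: the EuroQol-5D-5L figure of 130 is under-inflated (139–140 needed), and the GFR figure of 62 is evaluable pairs (83 with dropout)

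*Protocol article*

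**What the plan says.** The Sample size section sets one rule for all three primary endpoints: "All sample size calculations are performed for a significance level of 5%, power of 80%, and a dropout rate of 25" per cent. It then gives three figures.

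- **MAI score change:** 120 participants, for a difference of 3 points with SD 5, by t test.
- **Measured versus estimated GFR:** "Based on a paired *t* test, a sample size of 62 participants is required", for a difference of 4.0 mL/min/1.73 m² with SD 15 and R = 0.73. The same item adds that GFR is measured in every participant, whatever the allocation.
- **EuroQol-5D-5L:** by t test, "a sample size of 130 participants with or at risk of malnutrition is required to detect a clinically relevant difference of 0.15 points"; the SD of 0.27 is attached to the score change up to week 16, "assuming equal allocation in the two groups".

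The section then assumes that about 70% of patients will be at risk and concludes that "a total of 185 participants is required to achieve a sample size of 130 participants" with or at risk of malnutrition. Ethical approval covers 200. The abstract describes these as 130 at-risk patients and 70 others.

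Two other places bear on the point. The section on eligibility, recruitment and consent makes GFR measurement a separate consent option. The Statistical methods section analyses EuroQol-5D-5L by ANCOVA with the baseline score as covariate.

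**The concern.** The three figures sit under one stated dropout rule, yet they do not follow from it in the same way. A reader takes 130 and 62 as numbers to enrol that still give 80% power after a quarter of participants are lost.

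For EuroQol-5D-5L this matters because the planned at-risk group is 130, the calculated requirement itself. Any error in the inflation therefore passes straight into the power of a primary endpoint. For GFR, 62 is the number against which the trial would judge whether enough participants had agreed to the measurement.

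**Working it through.** **Inputs.** All are from the Sample size section: 5% significance, 80% power, 25% dropout, and the differences, SDs and correlation listed above. Sidedness is not stated. I assume two-sided tests and check that assumption in step 4. Sample sizes use the noncentral t distribution.

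**1. MAI (reference case).** Standardised difference 3/5 = 0.60. Required 44.6 per arm, so 45 per arm and 90 completers. Dropout: 90/0.75 = **120**. The plan's figure is reproduced exactly, with the correct inflation n/(1 − dropout).

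**2. EuroQol-5D-5L.** Standardised difference 0.15/0.27 = 0.556. Required 51.8 per arm, so 52 per arm and 104 completers.

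- 104 × 1.25 = **130**: the plan's figure, reproduced exactly.
- 104/0.75 = 138.7, so **139**, or **140** for equal arms (52/0.75 = 69.3, so 70 per arm).

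The stated figure multiplies by (1 + dropout) where it should divide by (1 − dropout). It does contain an allowance, but for 20% loss: 130 × 0.80 = 104. At 25% loss, 130 × 0.75 = 97.5 completers remain.

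| Completers | t-test power |
|---|---|
| 104 (20% loss of 130) | 80.1% |
| 98 | 77.7% |
| 97.5 (25% loss of 130) | 77.5% |
| 97 | 77.3% |

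**3. Measured versus estimated GFR.** SD of the paired difference = 15 × √(2 × (1 − 0.73)) = 11.02. Required 61.6, so **62** pairs. The plan's figure is reproduced with no dropout allowance at all. With the stated dropout, 62/0.75 = 82.7, so **83**.

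What the trial would have: GFR is planned in all 200, and 200 × 0.75 = 150 pairs give about 99% power. For 80% power to hold after 25% loss, 83 of 200 (42%) must consent to GFR measurement. The documents do not give the expected uptake.

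**4. Could another reading rescue the figures?**

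- One-sided testing gives 96 for MAI and 110 for EuroQol-5D-5L with the correct inflation (104 with × 1.25 per arm), so it reproduces neither 120 nor 130. It comes close to 62 for GFR alone (49 × 1.25 = 61.25), which does not make it a consistent reading.
- The normal approximation gives 102/0.75 = 136 for EuroQol-5D-5L, again not 130.

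**5. Derived total.** 130/0.70 = 185.7, which the plan gives as 185. With the corrected figures, 139/0.70 = 198.6 and 140/0.70 = 200, that is 199–200. The approved number is 200.

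**The case against.** **GFR.** One might infer that the GFR endpoint is underpowered: 62 participants with 25% loss leave 46–47 pairs and 67–68% power. The documents do not support that. Nothing limits GFR measurement to 62 people; the same item of the Sample size section plans it in everyone. The comparison is also made at a single time point, in hospital or within two weeks of discharge, so later follow-up losses do not erode it. Separate consent leaves some uncertainty about uptake, but power is at risk only if fewer than about 83 of 200 agree and a quarter of those are then lost. This part of the objection stands in full.

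**ANCOVA.** The 77% belongs to the planning t test, whereas the primary analysis adjusts for baseline. If 0.27 is the SD of the outcome before adjustment, power at 97.5 completers is 79.1% at a baseline correlation of 0.2 and 81.2% at 0.3. If 0.27 is the SD of the change score and the variances are equal at both visits, the residual variance is (1 + ρ)/2 of the change variance, and power is 88% at ρ = 0.5 and 84% at ρ = 0.7, falling below 80% only above about 0.87. The documents give no correlation, so these are assumed values. They show that the shortfall may be recovered, not that it is. The stated calculation still rests on a t test and does not deliver what it claims.

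**Slack in the at-risk group.** The recruitment section sets no explicit cap at 130, and 70% of 200 would be 140. That is fair, and it is why the correction is cheap. But the abstract plans 130 and the Sample size section names 130 as the requirement.

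**185 or 186.** The rounding of 185.7 is trivial and I do not press it.

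**Conclusion.** The point holds as an arithmetic inconsistency in two of the three stated figures.

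- **EuroQol-5D-5L:** 130 is under-inflated, not uninflated. It falls 9–10 participants short of the 25% rule. At that loss the planning t test has about 77% power in place of 80%, a gap of 2.5–3 percentage points that the baseline-adjusted analysis may close.
- **GFR:** 62 omits dropout and should read 83 if it is a number to enrol. This is a mislabelled requirement with no likely effect on power.
- **MAI:** 120 is correct.

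The conclusion assumes two-sided t tests, which the exact match to 120 supports, and takes the plan's SDs and correlation as given.

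**What to change.** In the Sample size section:

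1. State EuroQol-5D-5L as 139 (140 for equal arms) at 25% dropout. Alternatively, keep 130 and state that the t test has about 77% power at 25% dropout and 80% at 20%.
2. State the GFR requirement as 83 consenting participants, or label 62 as the number of evaluable pairs.
3. Update the derived total from 185 to 199–200 if the first option in item 1 is taken.
4. State that the tests are two-sided, if that is what was used.

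This is a text correction. At the plan's own 70% prevalence, 140 at-risk participants correspond to exactly the approved 200, and MAI needs only 120 of them, so no additional enrolment is needed. If recruitment is already complete (the article does not report its status), declaring the power that 130 gives is the option that remains.
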